## Protocol

### Study phases and design

Our funded programme of work is divided into three phases: (1) a prospective longitudinal clinical cohort study of acute medical admissions with nested health economics study and situational analysis, (2) co-creation of a complex intervention aiming at delivering improved care for people with multimorbidity and (3) a cluster randomised trial with nested process and economic evaluation to evaluate the intervention. This protocol focuses on phases 1 and 2. Phase 1 incorporates three distinct methodologies (see
Figure 1): 1 A) Prospective longitudinal cohort study; 1 B) health economic evaluation focussing on costs (patient and health-system) and consequences (health related quality of life); 1 C) patient-centred situation analysis with mixed qualitative methods including key informant interviews, focus group discussions and observation of patient care pathways. Phase 2 incorporates intervention cost-effectiveness modelling, to support co-creation, design and selection of an intervention to be evaluated subsequently through a cluster randomised clinical trial (phase 3).

**Figure 1. f1:**
[figure not shown]
Study layout. * qualitative study requires separate consent.

### Setting

This study will be conducted in four sites across two countries (Malawi and Tanzania). Within each country we will recruit patients from a central referral hospital and a district hospital to develop generalisable results, broadly applicable within both contexts. The study sites are: Queen Elizabeth Central Hospital, Blantyre, Malawi; 2) Chiradzulu District Hospital, Southern Region, Malawi; 3) Hai District Hospital, Tanzania; 4) Muhimbili National Hospital, Dar-es-Salaam, Tanzania. The study is planned to take approximately 15 months (12 months recruitment, with an additional three months to complete follow up) and will be conducted in parallel in all sites.

### Patient and Public Involvement

We partnered with established organisations working in the sphere of NCDs in Malawi and Tanzania. These include the Malawi and Tanzania NCD Alliances, Community for Disease Prevention and Management, Malawi Health Equity Network and community research advisory boards. These structures have direct contact with beneficiaries and community leaders. Prior to the development of the study, we conducted community forums with patients with NCDs, care givers, leaders of peer support groups and members of community research advisory board. These groups reflected on their experience with multimorbidity in their home, barriers and facilitators to diagnosis, treatment, and care for multimorbidity in health facilities and proposals for improvement. Their experiences informed the development of our situation analysis questions. We also engaged policy stakeholders from Ministries of Health in both countries in a need analysis process. This helped us to gain: the core national indicators for monitoring progress of NCDs and the status of their ongoing progress; national, local and community setup of structures for governing and managing NCD and multi-morbidity services: current NCD policies, programmes, and implementation strategies. Proposals and issues that came up from both the policy and community consultation will be part useful during the second and third stage of the study when we develop and implement the intervention (with continued engagement). The needs analysis helped in identifying key stakeholders whom to engage during this period as community and policy members from community advisory boards and national advisory groups.

### Participants

**
*Phase 1 A: Prospective longitudinal cohort study*.** Patients will be screened for enrolment at the primary point of entry for hospital admission. Cohort study participants will be consecutively recruited within 24 hours of emergency presentation, and stratified recruitment across four sites. Eligibility criteria are as follows:

Inclusion:

1.Adult patients (aged ≥18 years).2.Decision to admit to hospital.3.Physician diagnosis of an acute medical disorder.4.Residence within the study catchment area (predefined for each hospital site).5.Contactable on discharge by phone (either directly or through a carer).

Exclusion:

1.Pregnancy (other research groups are specifically addressing this).2.Planned medical admission.3.Detainees or prisoners.4.Admission for primary trauma, obstetric or gynaecological condition.5.Patient or carer declines consent to take part.

The study procedures and schedule for follow-up are described in
Table 1.

**Table 1. T1:** Study procedures and sampling schedule.

Study Visit	A	B	C	D	E	F	G
Day post admission	0	2	5	7	Discharge	30	90
Deferred consent	x						
Consent (verbal)	x	x	x	x	x		x
Consent (written)	3	3	3				
Vital signs (including blood pressure)	x	x	x	x	x		x
Medical history, function (including grip strength) and outcome assessment	x					4	x
Screen for Adverse Events (AEs)	x	x	x	x	x		x
HIV POC *	x						x
Where HIV, VL, urinary LAM, serum CrAg *	x						1
Blood glucose POC	x	x	x	x			x
HBA1c POC	x						x
Creatinine POC	x						x
Urinary dipstick	x						x
Serum save 5mL)	x						x
Situation analysis	x	x	x	x	x		x
Patient and health system costs					x	x	x
EQ5D questionnaire	x					x	x
Qualitative interviews					x		x

AE: adverse event; POC: point of care blood test; HIV: human immunodeficiency virus; VL: viral load; urine LAM: urinary lipoarabinomannan; CrAg: cryptococcal antigen; HbA1c: haemoglobin A1c (glycated haemoglobin). Additional contact with the participants may be made up to approximately 12 months after hospital admission to check the longer-term outcomes. This will be by telephone where possible. Visit F (hospital discharge) visit data will be collected, this may occur at any point before or after the 2, 5 and 7 day follow up visits. Visit G (90 day) will occur in a specific research outpatient follow-up clinic. There will be flexibility of ±10 working days for this follow up visit to take place. * Diagnostic HIV test and/or HIV viral load will be collected as part of routine clinical service. Parentheses indicate only if required to confirm diagnosis (rely on concurrent or earlier test). 1: Samples for urinary LAM and serum CrAg test will be collected and processed as part of routine clinical service to screen for opportunistic infection in line with WHO guidance at admission. 2: Qualitative interviews will take place with healthcare workers in a portion of treating providers after patient discharge. Qualitative interviews will take place with a proportion of patients after follow up visit at 90 days. 3: Written consent will be taken at the earliest possible opportunity, either directly from the patient or from a proxy (if patient lacks capacity). 4: Telephone or home visit follow-up (in order to maximise retention and data completeness)

**
*Phase 1 B: Health economic evaluation*.** One third of participants recruited to the cohort study will be randomised to the health economics study, with follow-up and data collection as per cohort study, or as detailed in section (Variables, below).

**
*Phase 1 C: Situation analysis*.** IDIs with patients and caregivers will include patients purposively sampled from the overall cohort whilst still an in-patient, at the point of hospital discharge or during the 90-day follow up clinic. Carers will include those supporting patients whilst they are being treated in hospital or who supported a patient who died (during their hospital stay or within 90 days after admission). During interviews, caregivers will be linked/matched to patients in approximately half of the cases (caregivers of the patients we will interview). This will help to diversify the data and facilitate recall for patients who may have experienced reduced capacity during the early stages of hospital admission.

FGDs will be conducted with patients who have recovered from acute medical admission and their caregivers, in the community, after hospital discharge. We will hold female and male specific FGDs to ensure equal participation, especially for women who may be inhibited from disclosure in the presence of men. We will approach and recruit the caregivers of acute medical patients (those staying full time with the patients at the hospital and providing day to day care) during their hospital admission. Patients and caregivers will take part in either FGD or in-depth interviews, but not both.

IDIs with healthcare workers and policy makers will include HCWs directly involved with acute medical patients – physicians (senior clinicians (consultants, juniors), nurses, ward attendants, reception clerks and/or frontline administrative staff. Policy makers will include those working in decision-making roles at the district and national hospitals and service delivery level of the government-funded health system.

Inclusion criteria

1.Patients (≥18 years) recruited from cohort study (separate consent sought for this sub-study).2.Carers/guardians caring for patients within the cohort study.3.Healthcare workers who provide direct care for patients recruited to the cohort study.4.Healthcare workers taking part in the training as part of the programme roll-out.5.Policymakers that have occupied their current or previous policymaker position for 3 months or more.

Exclusion criteria

1.Patients and carers who do not speak a language understood by one of the field research team (not anticipated, as team speak both English and the predominant local languages).2.Patients, carers and healthcare workers who are judged likely to be negatively affected by participation
*e.g.*, due to distress.3.Patients who are too sick to be out of bed and participate in an interview in a private area.4.Policymakers that are yet to be involved in policy development.

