*Phase 1 B: Health economic data sources and measurement*.** All consenting study participants will be asked asset ownership, house construction and demographic questions extracted from the most recent relevant national Demographic and Health Survey (DHS). Patient cost data will be captured before, during, and for 90 days after hospital admission using an amended version of the STOP-TB tool, a widely-used questionnaire for measuring TB patient costs
^
31
^. We will capture direct medical costs (
*e.g.*, drugs, diagnostics, consultation and inpatient fees), non-medical costs (
*e.g.*, food and transport), indirect costs (lost time for patients and guardians). Where a patient is readmitted to hospital, we will also capture these costs. Costs will be captured in local currency and presented in 2024 United States dollars.

Health system costs will be collected using top-down and bottom-up (micro) costing methods. We will develop and validate (with relevant hospital staff) a visual model of individual patient pathways through the study hospitals. This will be supplemented with data on waiting times, and time spent with various health workers from the sample of patients that are included in observations conducted as part of the situation analysis. Costs for each stage of the patient pathway (triage, admission, diagnostics, treatment, discharge, readmission
*etc*.) will be based on unit costs for tests, staff time, hospital bed days and other inputs, obtained from hospital data, tests and consumables suppliers, and Ministry of Health (MoH). Any other costs deemed relevant during the data collection stage will also be included. Top-down costing data on hospital overheads (utilities, building costs, maintenance,
*etc*.) will be obtained for each hospital.

HRQoL data will be collected using the EQ-5D-5L questionnaire in English, Chichewa (Malawi) and kiSwahili (Tanzania). The questionnaire will be administered, at admission, discharge, 30 and 90 days post admission in person or (day 30) by phone (as for patient costs).

**

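### The protocol gives no remote route to day-90 EQ-5D and outcome contact for participants who miss Visit G, and its sections disagree on telephone use at day 90

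*Protocol article*

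**What the plan says.** Participants, Table 1 and its legend, sets the schedule. In the row for history, function and outcome assessment, day 30 carries note 4 and day 90 carries a plain mark. Note 4 reads: "Telephone or home visit follow-up (in order to maximise retention and data completeness". For day 90 the legend says "Visit G (90 day) will occur in a specific research outpatient follow-up clinic", and "There will be flexibility of ±10 working days for this follow up visit to take place". It also provides that "Additional contact with the participants may be made up to approximately 12 months after hospital admission to check the longer-term outcomes", by telephone where that can be done.

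Data sources and measurement, Phase 1 B, gives the mode for EQ-5D as "30 and 90 days post admission in person or (day 30) by phone (as for patient costs". Variables, Phase 1 B, says that patient costs in the health economic subsample may be taken face to face or by phone at both 30 and 90 days.

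Data sources and measurement, Phase 1 A, has outcomes ascertained at discharge, day 30 and day 90. They are coded from a case summary and the medical notes to hand. For death alone it names every available record as a source.

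Every participant must meet the inclusion criterion "Contactable on discharge by phone (either directly or through a carer".

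**The concern.** The protocol recognises that remote contact protects completeness, but attaches it to the earlier time point and not to the later one, on which more depends. Change in health-related quality of life from admission to 90 days is part of the primary health economic objective. Survival, readmission and their composite at 90 days are secondary clinical objectives.

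Whether someone comes to a clinic at day 90 plausibly depends on how they are. Those who are disabled or back in hospital are less likely to attend, and those who have died cannot. If the text is followed literally, day-90 EQ-5D is absent for all of them. A readmission to another facility reaches the data only if it appears in notes that the team can see.

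Imputation may not repair this. The Analysis section plans chained equations with predictive mean matching and relevant baseline variables, which relies on data being missing at random given what is in the model. Deterioration between day 30 and day 90 that itself prevents attendance is not a baseline variable. A death that nobody records has a further effect: the QALY method assigns the death value from the date of death, so an unrecorded death would be handled as a missing questionnaire.

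**Working it through.** The protocol states no figure on this point, so the check sets its statements side by side.

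1. **Mode at day 90, by item**
   - History, function and outcome assessment: Table 1 has a plain mark, without note 4. The legend places the visit in a clinic. No remote option is stated.
   - EQ-5D: Data sources and measurement names phone for day 30 only. No remote option is stated.
   - Patient costs (health economic subsample): Variables allows telephone at 90 days.
   - Death: any available record may be used, so it does not depend on attendance alone.
   - Readmission: the general sources apply (case summary and medical notes), without the wider wording used for death.
   - Blood pressure, HbA1c, creatinine, dipstick and grip strength: these need the participant to be present.

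2. **Consistency.** The EQ-5D sentence restricts phone to day 30 and says the rule is the same as for patient costs. Variables has a different rule for patient costs. If the parenthesis describes the cost rule, it contradicts Variables. If EQ-5D is meant to follow the cost rule in Variables, the restriction to day 30 in the same sentence is wrong. A site cannot tell which applies.

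3. **Can the missing items be recovered otherwise?** EQ-5D cannot be taken from records afterwards. Dated death and readmission can be asked about later, and the provision for contact up to about 12 months would allow this. It is optional, however, is described as being for longer-term outcomes, and is not assigned to missed day-90 visits.

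4. **How much rests on the day-90 EQ-5D?** The Analysis section uses the area under the curve over admission, day 30 and day 90. Assume straight lines between these nominal days and write u0, u30 and u90 for the three values.
   - Area = 30 × (u0 + u30)/2 + (90 − 30) × (u30 + u90)/2 = 15 u0 + 45 u30 + 30 u90.
   - Weight of u90 = 30/90 = one third.

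   An added measurement at discharge before day 30 does not alter this weight. For change from admission to day 90, the day-90 value is the end point itself.

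5. **Size of any bias.** The documents give no day-90 attendance rate and no 90-day death or readmission rate. The only allowance for loss is in Sample size: 1600 − 1544 = 56, and 56/1600 = 3.5%. That is a drop-out margin for the prevalence estimate, not a forecast of attendance at Visit G. No bias can be computed from this.

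**The case against.** The strongest reply is that Visit G is a clinic visit for a good reason: it needs blood tests, blood pressure and grip strength, whereas day 30 does not. Saying where a visit takes place does not forbid ringing those who fail to come, and how missed visits are traced is detail that a condensed article may leave to the full protocol. Participants, Phase 1 B, also announces that health economic collection may depart from Table 1 as set out in Variables, so the telephone rule for costs is a declared exception.

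Much of this stands. The clinic setting is sensible, and silence about tracing alone would not be a finding. What remains is that the text does state the mode for EQ-5D, restricts phone to day 30, and equates this with a cost rule that reads differently elsewhere. The declared exception explains costs but leaves that mismatch unresolved.

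A reader might infer more: that 90-day survival is lost for non-attenders, or that telephone contact is allowed at day 30 and never after. The documents do not support either. Death may be coded from any available record. Telephone is allowed for 90-day costs and for optional contact up to about 12 months. The situation analysis plans interviews with carers of patients who died within 90 days, so the team expects to learn of such deaths. It is equally tempting to say that distant patients will be missed, but eligibility requires "Residence within the study catchment area (predefined for each hospital site", which weakens this. Nor can missed deaths be sized by comparing mortality in attenders and non-attenders: anyone seen at day 90 is alive by definition.

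**Conclusion.** The point holds as an inconsistency with a practical consequence. Followed literally, the protocol leaves day-90 EQ-5D uncollected in participants who miss Visit G, and exposes readmission to under-recording where it falls outside the notes to hand. Death at home is exposed to a lesser degree because of the wider record sources. That the missing participants would be sicker on average is plausible, but it is an assumption. The documents neither state nor exclude it, and the size of the effect is unknown. Loss of 90-day survival as such is not shown.

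The weight comes from day-90 quality of life, which is part of a primary objective. The clinical primary outcome, prevalence, is not in general affected; the Limitations section already acknowledges survivorship bias for chronic kidney disease, which depends on three-month data. According to Study status, follow-up was still open and analysis had not been done, so a correction can still be useful.

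**What to change.** Reconcile the Table 1 legend, Variables (Phase 1 B) and Data sources and measurement (Phase 1 B) so that they state one rule for day 90:

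- Participants who miss Visit G are contacted by phone, directly or through the carer, for vital status, readmission with dates, EQ-5D and, in the health economic subsample, patient costs.
- Physical and laboratory measures stay clinic-only.
- The mode of each EQ-5D administration is recorded.
- For participants who have already missed Visit G, the existing provision for telephone contact up to about 12 months is used to obtain dated death and readmission. Their day-90 EQ-5D cannot be recovered in this way and remains missing.

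The cost is some extra calls, using a procedure that already runs at day 30 and phone contact that was a condition of entry, plus changes of wording. The downside is a mixture of face-to-face and telephone EQ-5D at day 90, which recording the mode allows the analysis to examine.

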**Methods:**

This is a prospective longitudinal cohort study of adult (≥18 years) acute medical hospital admissions with nested health economic and situation analysis in four hospitals: 1) Queen Elizabeth Central Hospital, Blantyre, Malawi; 2) Chiradzulu District Hospital, Malawi; 3) Hai District Hospital, Boma Ng’ombe, Tanzania; 4) Muhimbili National Hospital, Dar-es-Salaam, Tanzania. Follow-up duration will be 90 days from hospital admission. We will use consecutive recruitment within 24 hours of emergency presentation and stratified recruitment across four sites. We will use point-of-care tests to refine estimates of disease pathology. We will conduct qualitative interviews with patients, caregivers, healthcare providers and policymakers; focus group discussions with patients and caregivers, and observations of hospital care pathways.

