### Objectives

The primary objectives of this mixed methods (clinical, health economics and qualitative) study are:

*Clinical:* Determine the prevalence of multimorbid disease in adults admitted to hospital with acute medical conditions in Malawi and Tanzania.

*Health Economic:* Measure economic costs incurred and changes in health-related quality of life between admission and 90 days post admission.

*Situation analysis:* Describe current care for multimorbidity, enabling and hindering factors to the delivery of patient centred care.

We aim to use the findings to inform the development and design of a randomised controlled trial.

The secondary objectives are:

*Clinical:*

1.Measure prevalence of important pre-selected individual conditions, including chronic non-communicable (hypertension, diabetes mellitus and chronic kidney disease) and communicable (HIV infection) conditions.2.Measure hospital readmission rate 30 and 90 days after admission.3.Measure survival 30 and 90 days after admission.4.Measure a composite of readmission free survival 30 and 90 days after admission.5.Measure markers of disease control 90 days after admission.6.Measure the rate of end-organ damage (such as cerebrovascular accident and myocardial infarction).

*Health Economic:*

1.Disaggregate economic costs from patient and health system perspectives and sub-analyse according to the presence of multimorbidity and other socio-economic factors.2.Model how patients with different multimorbidity incur costs as they pass through the health system.3.Analyse changes in Health-related Quality of Life according to presence of different diseases.4.Estimate the potential cost-effectiveness of a selected intervention to improve diagnosis and treatment for people with multimorbidity.

*Situation Analysis:*

1.Describe healthcare pathways for adults during and after acute medical admission using structured observational data during patient admission.2.Qualitatively describe (i) patients’ level of health literacy related to their own conditions and (ii) healthcare engagement for patients with multimorbidity using key-informant interviews.

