## Limitations

There are a number of limitations with this study, which we have attempted to mitigate. First, there are a limited number of sites in two countries. In order to generate broadly generalisable results, the chosen sites reflect a mix of tertiary / referral hospitals and district hospitals in each country. Second, we have decided to systematically screen for four conditions (HIV, hypertension, diabetes and CKD) using point-of-care diagnostics. This may miss multimorbidity from other chronic conditions, which require additional infrastructure to confirm diagnoses (such as clinical imaging or enhanced laboratories), but we will collect clinical data on all diagnosed chronic conditions. A recent systematic review indicates a high burden of disease from these four conditions among hospitals patients, which can importantly be diagnosed using available point-of-care tools
^
24
^. Third, CKD diagnoses require evidence of chronicity of disease at three months and therefore data in this condition is prone to survivorship bias. Fourth, EQ5D-5L data and resulting QALY estimates may not reflect the most accurate picture of HRQoL in our study context. However, through our eCRF, we will collect rich clinical data with additional scales (such as the Patient Health Questionnaire-9 [PHQ-9] screening tool for depression
^
34
^; and clinical frailty scale
^
35
^ to explore the possible limitations and interrelationships. Fifth, our planned situation analysis will provide a cross-sectional picture of the health system at the time of the study, which is not able to incorporate the dynamic and adaptive nature of health systems. However, the MultiLink consortium includes researchers from each country and site, with a rich understanding of the context.

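### The early half of the day-90 visit window conflicts with the protocol's own three-month rule for CKD and leaves part of the 90-day outcome period unseen for patients who attend early

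*Protocol article*

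**What the plan says.** All of this is in the protocol article; no analysis plan is shown.

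- **Visit timing.** Table 1 (Participants) counts visits from admission: "Day post admission 0 2 5 7 Discharge 30 90". The abstract's Methods agree: "Follow-up duration will be 90 days from hospital admission". The Table 1 footnote gives the 90-day visit a symmetric tolerance: "There will be flexibility of ±10 working days for this follow up visit to take place".
- **Kidney tests.** The Table 1 rows for creatinine and urinary dipstick each have two marks, which by column position fall at Visit A (day 0) and Visit G (day 90). No later sample is scheduled.
- **CKD rule.** Limitations: "CKD diagnoses require evidence of chronicity of disease at three months and therefore data in this condition is prone to survivorship bias".
- **Use of the CKD result.** The Sample size section takes 5% prevalence as the lower limit for including a disease in the intervention. It expects HIV, hypertension and diabetes to exceed that limit, and looks to the cohort to settle whether CKD is included.
- **90-day outcomes.** Objectives: "Measure hospital readmission rate 30 and 90 days after admission", survival at the same times, and "Measure a composite of readmission free survival 30 and 90 days after admission".
- **Other outcome sources.** Under Data sources and measurement, deaths are coded from every record available, and clinical outcomes from a case summary and the medical notes. The Table 1 footnote permits, but does not require, further contact up to about 12 months, by telephone where possible.

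**The concern.** A visit tolerance is harmless when the measurement does not depend on exact elapsed time. Here it does, in two ways.

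First, CKD is defined by persistence. All participants are acute admissions, so a raised creatinine at entry may reflect acute injury, and the second test is there to separate the two. If that test is taken about two weeks early, it does not meet the interval the protocol says is needed, and no later test is planned that could. An analysis plan can decide how to label such a result; it cannot supply a three-month creatinine that was never taken. The Introduction criticises earlier CKD data (7.7% prevalence) for lacking accurate information on chronicity, so this is a gap the cohort is well placed to close. At stake is the CKD prevalence that will be compared with 5%.

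Second, readmission, survival and their composite are fixed at 90 days. Visit G is the last scheduled outcome contact in Table 1. When it is early, the visit itself says nothing about the remaining days, and no contact at day 90 is fixed for those patients.

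**Working it through.** The protocol gives no figure of its own to reproduce on this point. The check is calendar arithmetic plus two illustrations.

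**1. Window in calendar days.** Inputs: nominal day 90; ±10 working days (both Table 1). On a five-day week, 10 working days = 2 weeks = 14 calendar days.
- Earliest: 90 − 14 = day 76. Latest: 90 + 14 = day 104.
- Checked over every admission date in one year, ignoring public holidays, the earliest permitted visit is day 76 to 78, by weekday of the target date, and the latest is day 102 to 104.

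**2. Kidney-test interval against the three-month rule.** Three calendar months is 89 to 92 days, by starting date.
- Shortfall for a day-76 visit: 89 − 76 = 13 days, to 92 − 76 = 16 days.
- With a window opening at day 90, a rule of at least 90 days is always met. A strict calendar reading can still fall short by up to 92 − 90 = 2 days.

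**3. What the CKD decision turns on.** As an illustration, compare the 7.7% cited in the Introduction with the 5% threshold at the target of 1600: (0.077 − 0.05) × 1600 = 43 patients. A few dozen classifications could therefore matter to the decision.

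**4. Unseen follow-up for the earliest attender.** Days 77 to 90 = 14 days; 14/90 = 15.6% of the period.

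The documents give no event rates, so assume a constant hazard over a range of true 90-day risks R, with risk by day 76 = 1 − (1 − R)^(76/90):

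| True 90-day risk | Risk by day 76 | Not seen at the visit |
|---|---|---|
| 10% | 8.5% | 1.5 points |
| 20% | 17.2% | 2.8 points |
| 30% | 26.0% | 4.0 points |
| 40% | 35.0% | 5.0 points |

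These apply only to patients seen at day 76, and only if no other source is used.

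**5. Average over all attenders, if visits were spread evenly over days 76–104 (an assumption).**
- Possible days: 104 − 76 + 1 = 29. Share before day 90: 14/29 = 48%.
- Mean unseen time: (1 + 2 + … + 14)/29 = 105/29 = 3.6 days; 3.6/90 = 4.0%.
- At a 20% 90-day risk, the daily hazard is −ln(0.8)/90 = 0.00248. The average loss is about 0.8 × 0.00248 × 3.62 = 0.7 points. The 95% half-width for 20% at n = 1600 is 1.96 × √(0.2 × 0.8/1600) = 2.0 points.

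**The case against.** The strongest reply is that a visit window is a scheduling tolerance and not a case definition. The only CKD rule the article states is the three-month one. If the authors apply it to actual test dates, early results will be left unconfirmed and no false CKD is created. That stands: nothing in the article says that an early abnormal result will be counted as chronic, though a reader might infer it. It does not remove the problem, because the early patients would then have no scheduled test able to confirm or exclude CKD.

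A reader might also infer that early attenders will be treated as event-free at day 90. The article states no such rule, and handling of incomplete follow-up is normally left to the analysis plan. Nor is Visit G the only source: deaths come from all available records, outcomes also from notes, being reachable by phone is an entry criterion, and later contact is possible. This reduces the outcome part considerably. What remains is that the later contact is optional and aimed at longer-term outcomes, so readmissions, and deaths outside the available records, can be missed.

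Extending the point to patient costs is not supported. The Variables section times cost collection from discharge and allows telephone, while other parts of the article time it from admission, so an early clinic visit does not by itself show that costs go unobserved.

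The direction of any net CKD error is also open. Counting unresolved acute injury as chronic would raise prevalence, but Limitations already acknowledges survivorship bias, which can lower it.

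**Conclusion.** The point holds for visits before day 90. For those patients the permitted window and the stated CKD requirement cannot both be satisfied by the scheduled tests, for the one condition whose inclusion the cohort is expected to decide. Showing this takes only one permitted early visit and a reading of three months as about 90 days.

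It does not hold for Visit G in general. A visit at or after day 90 covers the full outcome period and gives an interval of at least 90 days. For readmission and survival the finding is a smaller one: a risk of incomplete ascertainment, mainly of readmissions, covering at most about 14 of 90 days per patient.

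The total effect cannot be calculated, because the documents do not say how many visits are early. The 48% share and 3.6-day mean hold only under an even spread, and the share would be lower if sites tend to book late. Even under that spread, with a constant hazard, a 20% risk and no other source, the average outcome loss (0.7 points) is smaller than the sampling error (2.0 points). The CKD part is the main reason to act.

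**What to change.** The Study status section places the study in follow-up with analysis not yet done, so both parts below can still be carried out.

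**Remaining visits.** Open the Visit G window at day 90 and keep the late limit. State in days what interval counts as three months, so that the window and the CKD rule agree.

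**Visits already held early.**
- Classify kidney abnormality by the actual interval between the two tests. Report results short of the protocol's three-month rule as *chronicity not confirmed*, and show in a sensitivity analysis how CKD prevalence, and its position relative to 5%, changes when they are counted as CKD and when they are not.
- Confirm vital status and readmission at or after day 90 by telephone or from records. Where that fails, censor at last contact. The status check is preferable, because the logistic regression named in the Analysis section needs a known day-90 outcome and cannot use a censored one.

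**Cost.** Slightly later visits, one short call per early attender, an added reporting category, and possibly a minor amendment at the approving ethics bodies. Some patients will move to the unconfirmed group. No extra patients or tests are needed. The window change cannot help visits already completed, which is why the second part is needed.
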